# Comparison of heparin to citrate as a catheter locking solution for non-tunneled central venous hemodialysis catheters in patients requiring renal replacement therapy for acute renal failure (VERROU-REA study): study protocol for a randomized controlled trial

**DOI:** 10.1186/1745-6215-15-449

**Published:** 2014-11-19

**Keywords:** Citrate lock, Heparin lock, Catheter lock, Acute renal failure, Hemodialysis, Critically ill patient

## Abstract

**Background:**

The incidence of acute kidney injury (AKI) is estimated at 10 to 20% in patients admitted to intensive care units (ICU) and often requires renal replacement therapy (RRT). ICU mortality in AKI patients can exceed 50%. Venous catheters are the preferred vascular access method for AKI patients requiring RRT, but carry a risk of catheter thrombosis or infection. Catheter lock solutions are commonly used to prevent such complications. Heparin and citrate locks are both widely used for tunneled, long-term catheters, but few studies have compared citrate versus heparin for patients with short-term, non-tunneled catheters. We aim to compare citrate 4% catheter lock solution versus heparin in terms of event-free survival of the first non-tunneled hemodialysis catheter inserted in ICU patients with AKI requiring RRT. Secondary objectives are the rate of fibrinolysis, incidence of catheter thrombosis and catheter-related infection per 1,000 catheter days, length of stay in ICU and in-hospital and 28-day mortality.

**Methods/Design:**

The VERROU-REA study is a randomized, prospective, multicenter, double-blind, parallel-group, controlled superiority study carried out in the medical, surgical and nephrological ICUs of two large university hospitals in eastern France. A catheter lock solution composed of trisodium citrate at 4% will be compared to unfractionated heparin at a concentration of 5,000 IU/mL. All consecutive adult patients with AKI requiring extracorporeal RRT, and in whom a first non-tunneled catheter is to be inserted by the jugular or femoral approach, will be eligible. Catheters inserted by the subclavian approach, patients with acute liver failure, thrombopenia or contraindication to systemic anticoagulation will be excluded. Patients will be followed up daily in accordance with standard practices for RRT until death or discharge.

**Discussion:**

Data is scarce regarding the use of non-tunneled catheters in the ICU setting in patients with AKI. This study will provide an evidence base for recommendations regarding the use of anticoagulant catheter locks for the prevention of dysfunction in non-tunneled hemodialysis catheters in patients with AKI in critical or intensive care.

**Trial registration:**

Registered with Clinicaltrials.gov (registration number: NCT01962116) on 27 August 2013.

## Background

The incidence of acute kidney injury (AKI) varies according to the populations studied and the definition used, but it is estimated to be around 10 to 20% in patients admitted to the intensive care unit (ICU) [1–3]. The cause of AKI is most commonly acute tubular necrosis occurring in the context of shock (septic and/or cardiogenic), or drug toxicities (such as aminoglycosides or contrast medium). The pathophysiology of AKI is well established, and includes vascular, medullar and tubular injury leading to a reduction in the rate of glomerular filtration, and ultimately, anuria [4]. Renal replacement therapy (RRT) can be required, depending on the AKI etiology and comorbidities, particularly pre-existing renal insufficiency. In one observational study carried out among almost 30,000 ICU patients, the rate of RRT was around 4% [3], but rates as high as 70 to 80% have been reported in patients with shock [5–7]. Mortality in the ICU ranges from 15 to 25%, but can reach 50 to 60% in patients with AKI [3, 8].

Venous catheters are currently the preferred vascular access method for patients with AKI requiring extracorporeal RRT [9, 10]. In critical care, non-tunneled catheters represent standard practice. Despite the vast progress in the management of AKI and high-quality catheter practices [11–13], vascular access remains the weak link in the chain of RRT and contributes to increased morbidity in hemodialysis patients, particularly through catheter dysfunction (stenosis and/or thrombosis) and infection.

Strategies to prevent hemodialysis catheter dysfunction and infection include catheter locks, which are generally either heparin or citrate. The principle of the catheter lock is to instil an anticoagulant solution into the lumen of the branches of the hemodialysis catheter after each RRT session, leaving them in place until the next session.

Heparin locks are considered as the reference for non-tunneled hemodialysis catheters, and are indicated in the setting of RRT. Heparin exerts its anticoagulant effect by binding to antithrombin and antagonizing anti-Xa and anti-IIa activity, as well as all activated coagulation factors. The anticoagulant effect of heparin renders it difficult to handle in the ICU because of the associated bleeding risk [14–16] and the risk of heparin-induced thrombocytopenia [17–19]. Fibrinolysis *in situ* in the catheter has been reported to be necessary in 3 to 9.5 per 1,000 catheter days, reflecting the failure of anticoagulation and the wide variations in heparin concentrations within the catheter that can be observed with this drug [20, 21].

Citrate is an alternative to heparin as a catheter lock solution. Citrate exerts its anticoagulant effect by its ability to chelate calcium, which is fundamental to the activation of the coagulation cascade, but also of platelet activity [22, 23]. Citrate can prevent the formation of a biofilm by calcium and magnesium chelating effects, thus avoiding bacterial colonization [24–28]. Trisodium citrate 4% is considered as the reference lock solution for long-term tunneled catheters in patients undergoing chronic hemodialysis, in order to prevent catheter dysfunction and infection [29, 30]. It is noteworthy that in 2000, the Food and Drug Administration prohibited the use of citrate at concentrations greater than 4% due to the risk of metabolic disorders [31, 32], notably major hypocalcemia resulting in death [33] in cases of systemic leakage. Conversely, bacterial resistance has never been reported with citrate when used as a catheter lock solution.

There are few data from the literature reporting comparisons between citrate and heparin locks for patients with non-tunneled catheters. Data mainly concern patients undergoing chronic RRT with long-term tunneled catheters. These predominantly favored citrate locks for the prevention of infectious and thrombotic risk [28, 34–37].

To the best of our knowledge, only one randomized study, which included 291 patients, has compared the safety and efficacy of heparin versus citrate as a locking solution for non-tunneled catheters in hemodialysis patients [15]. The risk of catheter dysfunction was significantly lower in the citrate group, at 5 versus 8.1 events per 1,000 catheter days for citrate versus heparin respectively (relative risk (RR) 0.38, *P* = 0.015). The authors also noted a lower incidence of catheter infection in the citrate group (1.4 out of 1,000 catheter days) as compared to the heparin group (3.9 out of 1,000 catheter days) (RR 0.36, 95%CI 0.13 to 1.00, *P* = 0.05). Furthermore, the risk of bleeding and death from catheter-related bacteremia was significantly lower in the citrate group. Indeed, it should be noted that this study was prematurely interrupted because of a significant difference in catheter-related bacteremia between groups, in favor of the citrate group. Nevertheless, in this same study, the citrate concentration used was 30% (instead of 4%), and patients in intensive or critical care were excluded.

The primary objective of our study is to demonstrate the superiority of trisodium citrate 4% over heparin as a catheter lock solution, in terms of event-free survival of the first non-tunneled hemodialysis catheter inserted in patients hospitalized in intensive or critical care for AKI requiring extracorporeal RRT. Secondary objectives are to compare the rate of fibrinolysis, incidence of catheter thrombosis and catheter-related infection per 1,000 catheter days, length of stay in an ICU, and in-hospital and 28-day mortality.

## Methods/Design

### Study design

The VERROU-REA study is a randomized, prospective, multicenter, double-blind, parallel-group, controlled superiority study. The study is carried out in the medical ICU, the neuro-trauma ICU and the nephrology ICU of the University Hospital of Dijon, France, and in the medical ICU, the surgical ICU, and the nephrology ICU of the University Hospital of Besancon, France. Two strategies will be compared. Firstly, the treatment under study is a catheter locking solution composed of trisodium citrate at 4% (Citra-Lock, Dirinco AG, Bern, Switzerland). This treatment is not currently approved for use in the context of extracorporeal RRT in critically ill patients with non-tunneled catheters. However, there are international recommendations for its use in chronic dialysis patients with tunneled catheters [29, 30]. Secondly, in the control group, the catheter lock used will be unfractionated heparin at a concentration of 5,000 IU/mL, used within the range of its currently approved indications, namely prevention of coagulation in catheters used for extracorporeal circulation and RRT.

### Study population

All consecutive patients, hospitalized in any one of the participating units, with AKI requiring extracorporeal RRT will be included in the study. Patients are screened daily by the clinical research monitors and investigators in each center.

#### Inclusion criteria

The inclusion criteria for the study are as follows: patients aged over 18 years, in whom a first non-tunneled catheter is to be inserted by the jugular or femoral approach by medical staff in the participating department.

#### Exclusion criteria

The exclusion criteria are as follows: catheters inserted by the subclavian approach, patients with a contraindication to systemic anticoagulation (active uncontrolled bleeding, acute liver failure (Factor V < 30%), thrombopenia < 30,000/mm^3^ in the absence of planned correction), documented or suspected heparin-induced thrombocytopenia, known allergy to citrate, documented systemic bacterial infection not under treatment at the time of randomization, patients not affiliated with a health insurance system (beneficiary or dependent), pregnant patients or legally protected adults (namely adults in lawful custody or requiring assistance in the conduct of their own affairs or in respect of whom power of attorney is registered).

### Study conduct

Inclusions in the study started on 14 June 2013. All staff likely to be involved in the management of patients included in the VERROU-REA study have attended a training session to undergo training in the monitoring procedures, and posters outlining the main procedures to remember are on permanent display in all participating departments. Time zero is when randomization is performed.

#### Randomization procedure

Randomization will be performed directly through the secure Tenalea™ internet-based software (Formsvision BV, Abcoude, Netherlands) after identification of the investigator by a personal password, which will be communicated prior to initiation of the study. The treatment algorithms have been determined by the study statistician (Clinical Investigation Centre - Clinical Epidemiology/Clinical Trials (CIC-EC), Dijon, France). The allocation is based on a minimization technique taking into account the catheter insertion site (jugular or femoral), type of dialysis (continuous or intermittent) and Simplified Acute Physiology Score (< 55 or ≥ 55) [38]. Patients are assigned to treatment groups (citrate or heparin) using block randomization stratified by center. A comprehensive document describing the randomization procedure is kept in a confidential manner at the CIC-EC of Dijon.

#### Preparation of catheter locks at the hospital pharmacy

Both catheter lock solutions under study are prepared by the pharmacy of Dijon University Hospital and provided to the pharmacy of the participating hospital, with specific labels identifying the study, and in their original packaging, for storage in each participating department in the usual conditions according to the treatment attributed by randomization. The presentation of both solutions (heparin and citrate) is identical (5 mL syringe). Special labels indicating the regulatory information regarding the clinical trials are provided by the pharmacy of the University Hospital of Dijon and stuck to the syringe by the nurse who prepares the catheter lock solution.

Reception, dispensing and return of study drugs will be documented in writing in a dedicated study file kept in the pharmacy. Units of unused study drug will be returned to the pharmacy by the investigator after withdrawal of the first catheter. Since the study is a double-blind design, the investigators are unaware of the type of lock solution being instilled in the catheter for each patient. To preserve the blinding, the lock solution is provided in a box. The preparation to be injected as catheter lock is prepared in a 5 mL syringe by a nurse from the unit, in isolation in a specific room dedicated to the study procedures. The nurse then provides the pre-prepared syringe to the physician in charge of the patient’s management, who injects the lock solution slowly into the catheter lumen. In order to keep the blinding intact, the nurse who prepares the syringe with the catheter lock is not in charge of the patient’s management.

#### Study treatments

Citrate or heparin, according to the study group, will be instilled into each lumen of the catheter to attain a total volume corresponding to the volume of each branch according to the Summary of Product Characteristics. Before each administration of citrate or heparin, the catheter lumens will be flushed with 10 mL of saline as quickly as possible. Then, the lock solution (heparin or citrate) will be injected slowly (over at least 10 seconds duration) into each lumen.

Before initiation of RRT and use of the catheter, a minimum of 5 cc of liquid will be extracted from each lumen (volume greater than the contents of each lumen). Catheter patency will be verified by performing a blood return with a 20 cc syringe. If the 20 cc syringe fills smoothly in under four seconds, this corresponds to a blood flow of 300 mL/min on the hemodialysis machine. All catheters used will have a minimum diameter of 13.5 French. Only one catheter per patient will be considered for the study analysis.

#### Patient management

Daily monitoring of all patients will be performed in accordance with standard practices for patients undergoing RRT. Hemodialysis catheters will be used for the purpose of RRT only (no infusions will be administered through the catheters). For hemodialysis catheter management, two nurses will be present. One will work in aseptic conditions (as for an operating theatre) to manage RRT initiation (withdrawal of lock solution, patency check by blood return and connection of the dialysis lines to the catheter) and completion (remove dialysis lines, flush catheter, insert catheter lock solution and bandage). The second nurse will oversee the control panel and working of the dialysis machine. Hemodynamic monitoring of the patient is performed continuously during RRT, including monitoring of dialysis circuit pressures and transmembrane pressure.

Signs of thrombosis are recorded every time the catheter is connected to the dialysis machine. Signs of infection are recorded several times daily, with measurement of the patient’s temperature every three hours and daily surveillance of the puncture site. Samples will be obtained by swabbing the skin in case of suspected infection, in addition to blood samples. In case of suspected or confirmed infection, the catheter will systematically be removed and the need for antibiotic therapy will be discussed by the medical team. If and when identified, the germs responsible for the infection will be noted. Bleeding complications will also be recorded, defined as a drop in hemoglobin levels requiring transfusion of at least two packs of red blood cells, in cases of major bleeding, and number of packs of red blood cells transfused.

Insofar as possible, the catheter will be removed before patient discharge. Patients will be followed up for the duration of their hospital stay.

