#### Data collection

All data will be recorded daily in the dedicated case report form for the entire duration of the study. The following data will be recorded:for each patient: Simplified Acute Physiology Score II, Sequential Organ Failure Assessment score at randomization, demographic data (age, sex, weight, height, comorbidities, clinical and microbiological data to confirm the diagnosis of catheter-related infection (if any)), monitoring (type of RRT, continuous or intermittent RRT, duration of each RRT session and use of systemic anticoagulant) and general complications (bleeding, thrombosis or systemic infection).for each catheter: insertion date, insertion site, catheter removal date, reason for catheter withdrawal, use of ultrasound guidance, experience of the operator (junior, (resident in training), senior with under two years’ experience or senior with more than two years’ experience), need for antibiotic therapy due to suspected or confirmed catheter infection, puncture site bleeding, hematoma, thrombosis, local signs of infection and microbiology (catheter culture, puncture site culture and blood culture).

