#### Secondary endpoints

Secondary endpoints are: the rate of fibrinolysis per 1,000 catheter days, the incidence of catheter dysfunction per 1,000 catheter days, the incidence of catheter-related infection per 1,000 catheter days, the number of hemorrhagic events requiring the transfusion of at least two units of packed red blood cells, length of stay in intensive or critical care, length of hospital stay and in-hospital and 28-day mortality rate.

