### Sample size calculation

The sample size was calculated using PASS software (version 11, Kayesville, Utah, United States), based on several assumptions. The study by Hermite *et al*. [41] compared the event-free survival of catheters with citrate locks versus saline solution in ICU patients with an indication for extracorporeal RRT. In this study, the median duration of catheter survival with citrate locking solution was 12 days (interquartile range (IQR): 8 to 17], versus six days [3–10] for catheters locked with saline solution (hazard ratio (HR): 2.12, 95% confidence interval (CI): 1.32 to 3.4), *P* = 0.0019). The study by Weijmer *et al*. [15] reported an RR of 0.69 (95%CI: 0.44 to 1.08), *P* = 0.11) for premature withdrawal of non-tunneled, uncuffed catheters with citrate versus heparin. On the basis of these findings, in the prudent hypothesis of a reduction of 25% in the risk of catheter-related events (median of 12 days in the citrate group versus nine days in the heparin group), at an alpha risk of 5% and a beta risk of 20%, a total of 366 patients (183 per group) is required. Accounting for possible crossovers between groups (less than 5% switching from heparin to citrate) due to heparin-induced thrombocytopenia, and allowing for patients lost to follow-up, the final sample size is calculated to be 386 patients (193 patients included per group).

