#### Secondary objectives

Secondary endpoints will be compared using the chi square test, Fisher’s exact test, Student’s t-test, or the Mann-Whitney U test, as appropriate. Treatment effects will be presented with 95% CI. All analysis will be performed using SAS version 9.2 (SAS Institute Inc., Cary, North Carolina, United States).

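### 28-day mortality is listed as a secondary endpoint, but the stated follow-up ends at death or hospital discharge and nothing provides for vital status at day 28 after discharge

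*Protocol article*

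**What the plan says.** **Endpoint.** The Secondary endpoints section ends its list with "length of hospital stay and in-hospital and 28-day mortality rate". The last paragraph of Background gives the same pair among the secondary objectives ("length of stay in an ICU, and in-hospital and 28-day mortality"), and so does the abstract. In each place the two mortality measures stand side by side as different quantities.

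**Follow-up.** The abstract's Methods/Design paragraph states: "Patients will be followed up daily in accordance with standard practices for RRT until death or discharge". The Patient management section closes with "Patients will be followed up for the duration of their hospital stay".

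**Time origin.** Study conduct says "Time zero is when randomization is performed". Day 28 is not anchored explicitly, but randomization is the only time zero given.

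**Analysis.** For all secondary endpoints: "Secondary endpoints will be compared using the chi square test, Fisher’s exact test, Student’s t-test, or the Mann-Whitney U test, as appropriate".

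**The concern.** A mortality proportion at a fixed day needs each patient's vital status on that day, wherever the patient then is. Follow-up that ends at discharge supplies this for patients who die in hospital by day 28 and for those still in hospital on day 28. It does not supply it for patients who leave alive earlier. Because in-hospital mortality is a separate endpoint, 28-day mortality cannot be taken as another name for it.

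The analyst then has to choose, and the article does not say which choice applies. One choice is to count early-discharged patients as alive, which answers a different question from the one named. The other is to drop them, which removes only patients who left alive and so enriches the denominator with deaths. The two choices bias the result in opposite directions. Readers are likely to quote mortality from an intensive care trial, so the label should match what is measured.

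**Working it through.** **Step 1: the text.**

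| Question | What the article provides |
|---|---|
| When must status be known? | Day 28, for every patient (Secondary endpoints) |
| When does follow-up end? | Death or discharge (abstract); end of hospital stay (Patient management) |
| Is there contact or a record check after discharge? | None described in any section |
| Is there a rule for patients discharged before day 28? | None described |
| Which test applies to a binary secondary endpoint? | Chi square or Fisher, which needs a known status for each patient analysed |

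Data collection says "All data will be recorded daily in the dedicated case report form for the entire duration of the study". This does not close the gap, because each patient's own follow-up is tied to the hospital stay.

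**Step 2: possible size.** The plan gives no figure of its own to reproduce. The inputs are:

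- *N* = 386, the planned total (Sample size calculation).
- *m* = 50 to 60%, in-hospital death by day 28. This is an assumption borrowed from Background, which says ICU mortality can reach that range in acute kidney injury. It is neither a 28-day figure nor one for this trial.
- *f* = 10 to 50%, the share of the remaining patients discharged before day 28. Assumed.
- *r* = 2 to 10%, the risk of death between discharge and day 28. Assumed.

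The formulas are:

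- Patients with unknown status: *N* × (1 − *m*) × *f*.
- Understatement if they are counted as alive: (1 − *m*) × *f* × *r*.
- Reported proportion if they are excluded: *m* / [1 − (1 − *m*) × *f*].
- True proportion: *m* + (1 − *m*) × *f* × *r*.

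| *m* | *f* | Unknown status | Counted alive: understated by (*r* 2% to 10%) | Excluded: reported | Excluded: overstated by (*r* 10% to 2%) |
|---|---|---|---|---|---|
| 50% | 10% | 386 × 0.5 × 0.1 = 19.3 (5%) | 0.1 to 0.5 points | 0.5/0.95 = 52.6% | 2.1 to 2.5 points |
| 50% | 50% | 386 × 0.5 × 0.5 = 96.5 (25%) | 0.5 to 2.5 points | 0.5/0.75 = 66.7% | 14.2 to 16.2 points |
| 60% | 10% | 386 × 0.4 × 0.1 = 15.4 (4%) | 0.08 to 0.4 points | 0.6/0.96 = 62.5% | 2.1 to 2.4 points |
| 60% | 50% | 386 × 0.4 × 0.5 = 77.2 (20%) | 0.4 to 2.0 points | 0.6/0.80 = 75.0% | 13.0 to 14.6 points |

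About 15 to 96 patients would therefore have unknown status. Missed deaths would run from 15.4 × 0.02 = 0.3 to 96.5 × 0.10 = 9.7.

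**Step 3: sensitivity to *m*.** With *m* = 40% and the same *f* and *r*, the ranges are 386 × 0.6 × 0.1 = 23 to 386 × 0.6 × 0.5 = 116 patients, and 0.12 to 3.0 points of understatement.

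**The case against.** The best defence is that the two follow-up sentences may describe bedside surveillance only. The abstract speaks of daily follow-up under usual dialysis practice. The Patient management sentence comes straight after one about removing the catheter before discharge. A single status check at day 28 could coexist with daily monitoring that stops at discharge, and a condensed article may leave that check to the full protocol. Nor is the Data collection list a complete inventory: it also omits discharge dates, in-hospital death and fibrinolysis, all of which other secondary endpoints need. Its silence about day 28 therefore proves little.

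Much of this stands. A reader might infer that 28-day mortality cannot be determined in this trial. The documents do not support that, because nothing rules out a later status check. What remains is that the article states the end of follow-up twice, with no exception, and that this end does not fit an endpoint it also states. That goes beyond omitted detail.

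Two other inferences are tempting and should be resisted.

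- *Missing status differs by arm because the lock changes time to discharge.* Length of stay is a secondary endpoint, so the route is conceivable. But the documents give no figure for such an effect, and the double-blind design makes discharge decisions that depend on arm less likely.
- *A much larger loss, for instance 40% of all patients (0.40 × 386 = 154).* At 50 to 60% mortality only 193 to 154 patients survive, so 154 early discharges would be 80 to 100% of all survivors. That is an extreme bound.

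**Conclusion.** The endpoint and the follow-up window, as written, do not match. The gap is confined to patients discharged alive before day 28 and to this one secondary endpoint. The primary endpoint, the primary and interim analyses and the sample size are unaffected.

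Under the stated assumptions, counting these patients as alive costs little, about 0.1 to 2.5 percentage points of mortality. Excluding them would distort more, by about 2 to 16 points upward. Both ranges rest on assumed rates of discharge and of later death, and on a mortality range taken from the background literature; the trial's own values could lie elsewhere. The mismatch itself does not depend on any of these numbers. It merits correction as a modest point of consistency, not as a threat to the trial's main conclusion.

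**What to change.** Reconcile the abstract's Methods/Design paragraph and Patient management with Secondary endpoints, in one of two ways.

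1. **Keep the endpoint.** State that vital status at day 28 after randomization is ascertained for every patient, including those discharged or transferred earlier, by telephone or record query. Apply this also to patients already enrolled: Trial status reports 191 recruited at submission, leaving 386 − 191 = 195 to be covered prospectively. The cost is one query per early-discharged patient and one case report form field.
2. **Rename the endpoint.** If no such check will be made, call it in-hospital death by day 28 in the abstract, in Background and in Secondary endpoints. This costs only wording, but the result then differs from in-hospital mortality only by hospital deaths after day 28, and it should not be compared with true 28-day mortality from other studies.

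The first option is preferable because it preserves the endpoint the trial set out to report.
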